**Interim Analysis**

After 15 participants in each group are studied, an interim analysis will be conducted to determine if a further 21 participants/group are required to be studied.

# Regulatory Issues

**Non-CTIMP Status**

A previous version of this protocol (Version 1, dated 6 July 2009) was submitted to the MHRA, who advised that this research project does not constitute a Clinical Trial of an Investigational Medicinal Product (IMP) as defined by the EU Directive 2001/20/EC.

**Ethical Approval**

The Chief Investigator has obtained approval from the Hertfordshire Research Ethics Committee. The study has been submitted for Site Specific Assessment (SSA) at Cambridge University Hospitals NHS Foundation Trust. The study will be conducted in accordance with the recommendations for physicians involved in research on human subjects adopted by the 18th World Medical Assembly, Helsinki 1964 and later revisions.

**Consent**

Informed consent to enter the study will be sought from each participant only after a full explanation has been given, an information leaflet offered and time allowed for consideration. Signed participant consent will be obtained. The right of the participant to refuse to participate without giving reasons will be respected. All participants are free to withdraw at any time from the protocol treatment without giving reasons and without prejudicing further treatment.

**Confidentiality**

The Chief Investigator will preserve the confidentiality of participants taking part in the study and is registered under the Data Protection Act.

**Indemnity**

NHS Indemnity will apply to any claims made against Cambridge University Hospitals NHS Foundation Trust for negligent harm. There is no cover for non-negligent harm.

##

**Sponsor**

Cambridge University Hospitals NHS Foundation Trust will act as sponsor for this study.

**Funding**

This study is funded from Clinical Pharmacology department funds.

# Appendix 1. Summary of investigations, treatment and assessments

|  | **VISIT 1**  Screening  (Day -28 to Day -1) | **VISIT 2**  Randomisation  (Day 0) | **VISIT 3**  End of Treatment  (Day 56) | **FOLLOW-UP**  (telephone screen)  (Day 70) |
| --- | --- | --- | --- | --- |
| Informed Consent | X |  |  |  |
| Medical History | X |  |  |  |
| Physical Examination | X |  |  |  |
| Height | X |  |  |  |
| Weight | X | X | X |  |
| Blood Tests |  | X^[[1]](#footnote-1)^ | X1 |  |
| Urine pregnancy test (women of CBP) | X |  |  |  |
| Urine test (isoprostanes) |  | X | X |  |
| 12-lead ECG | X | X | X |  |
| Blood pressure & vitals | X | X | X |  |
| Arterial stiffness measurements |  | X | X |  |
| Inclusion/exclusion criteria checks | X | X |  |  |
| Randomisation |  | X |  |  |
| Provision of study medication |  | X |  |  |
| Forearm blood flow studies |  | X | X |  |
| Adverse Events |  | X | X | X |
| Concomitant Medications | X | X | X |  |

1. 50ml of venous blood will be drawn for estimation of plasma lycopene, standard haematology/chemistry (to include urea and electrolytes, hsCRP, full cholesterol profile), endothelial progenitor cells, oxidised LDL, and other biomarkers of inflammation (eg LDL oxidating activity, AtheroAbzymes, CRP, lipoprotein profile, adiponectin, TNF, IL-2, IL-6, Endothelial Progenitor and Endothelial Shedded Cells). [↑](#footnote-ref-1)

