**Exclusion criteria (Healthy Group)**

- Hypertension (Sustained BP>160/100mmHg), or other cardiovascular disease
- Use of a statin within the preceding three months, or at study start
- Significant renal, respiratory or neurological disease
- Diabetes mellitus
- BMI>32 kg/m^2^, BMI<18 kg/m^2^
- Pregnant or taking the combined oral contraceptive pill or hormone replacement therapy
- Use of vasoactive or other medication including regular NSAIDs
- Use of heparin or warfarin
- Allergy to tomato or tomato products
- Lactose intolerance
- Allergy to whey protein or soy protein
- Any concomitant condition that, at the discretion of the investigator, may affect the participant’s ability to complete the study
- Lack of informed consent
- Current involvement in other research studies

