**Study Visits**

**Screening – Visit 1 (Days -28 to -1)**

Informed consent, medical history, physical examination, height and weight, 12 lead ECG, BP and other vitals, pregnancy testing (urine) for women of child-bearing potential, concomitant medications. Home blood pressure measurements to be taken morning and evening on 7 days between Visit 1 and Visit 2.

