**Visit 2 (Day 0)**

Randomisation. BP and vitals, concomitant medications, weight, arterial stiffness measurements, 12 lead ECG, blood sampling, urine sampling, then forearm study. First dose to be taken that evening.

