**Urine Sampling**

A sample of urine will be collected for measurement of isoprostanes.

Arterial stiffness measurements

Measurements will be made using a non-invasive tonometer applied to the carotid, radial and femoral arteries in the seated and supine position for measurement of pulse wave analysis and aortic pulse wave velocity.

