# Forearm blood flow studies

Forearm blood flow will be measured simultaneously in both arms using venous occlusion plethysmography with mercury-in-silastic strain gauges electrically calibrated. The laboratory will be quiet and the temperature will be controlled at 23 ± 2OC. A 27 gauge un-mounted steel needle will be inserted into the non-dominant brachial artery under local anaesthesia (1% lignocaine hydrochloride). Saline or drugs will be infused at a constant rate of 1.0 ml/min by means of a constant rate infusion pump. Basal blood flow will be recorded after 30 min of saline infusion. Acetylcholine (7.5 & 15 µg/min) will then be infused intra-arterially at 1 ml/min as a measure of endothelial NO activity. Each dose will be infused for 6 minutes and forearm blood flow will be measured for 3 minutes at the end of each infusion period. The means of these measurements will be used for analysis. After a further 30 min washout with

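### Pregnancy is tested for only at screening, so at randomisation and the first intra-arterial study the result can be up to 28 days old, although eligibility is re-checked that day

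*Protocol*

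**What the plan says.** Both exclusion lists in the Protocol carry the same entry: "Pregnant or taking the combined oral contraceptive pill or hormone replacement therapy". The test behind it appears in two places, which agree. The screening visit text lists "pregnancy testing (urine) for women of child-bearing potential", and the row in Appendix 1 reads "Urine pregnancy test (women of CBP) | X", with nothing in the columns for Visit 2, Visit 3 or follow-up.

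The entry criteria are looked at twice, at Visits 1 and 2: "Inclusion/exclusion criteria checks | X | X". Visit 2 is Day 0. Its text puts randomisation first in the list and ends with "blood sampling, urine sampling, then forearm study". No pregnancy test is listed there. According to the Urine Sampling section, the urine taken at that visit has another purpose: "A sample of urine will be collected for measurement of isoprostanes".

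The forearm study is the invasive part of the trial: "A 27 gauge un-mounted steel needle will be inserted into the non-dominant brachial artery under local anaesthesia". Acetylcholine, sodium nitroprusside and L-NMMA are then infused. It is done at Visits 2 and 3.

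On timing, screening may fall anywhere from Day -28 to Day -1, with one further constraint: "Home blood pressure measurements to be taken morning and evening on 7 days between Visit 1 and Visit 2".

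**The concern.** Repeating the eligibility check on Day 0 shows that the protocol means the criteria to hold on the day of randomisation. For pregnancy, it provides a specific test but does not attach that test to the second check. Asking the participant can bring out a known or suspected pregnancy. It cannot bring out one of which she is unaware.

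If the plan is followed exactly, a woman whose pregnancy began, or first became detectable, after Visit 1 could therefore be randomised and have an arterial needle and three vasoactive agents on the strength of an outdated negative result. The protocol does not say whether pregnancy is excluded for the participant's safety or because it alters vascular function. The gap matters under either reason: the exclusion is confirmed by test only as of screening, not as of entry. The combined pill is also an exclusion, and the document states no contraception requirement, so it shows no other safeguard. Any advice in the participant leaflet is not available here and is not judged.

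**Working it through.** The protocol gives no figure for the age of the test, so there is none to reproduce. The check is day arithmetic on the visit windows.

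**Inputs**
- Visit 1, with the only test: Day -28 to Day -1 (screening visit text and Appendix 1).
- Home blood pressure: 7 days of readings between Visits 1 and 2 (screening visit text).
- Visit 2, with randomisation and the first forearm study: Day 0.
- Visit 3, with the second forearm study: Day 56 +/- 7, that is Day 49 to Day 63.

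**Formula**

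Age of the test at a visit = day of that visit minus day of Visit 1.

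**Visit 2**
- Oldest: 0 - (-28) = 28 days. This follows directly from the stated window.
- Youngest, from the window alone: 0 - (-1) = 1 day.
- Youngest, leaving room for 7 home blood pressure days: 0 - (-7) = 7 days. If all 7 must lie strictly between the visits, Visit 1 is no later than Day -8, and 0 - (-8) = 8 days.

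The working range is about 7 to 28 days. The upper end is stated by the protocol; the lower end is an inference.

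**Visit 3, for information**
- On Day 56 exactly: 56 + 7 = 63 to 56 + 28 = 84 days.
- Over the allowed window: 49 + 7 = 56 to 63 + 28 = 91 days. The screening window alone would put the lower end at 49 + 1 = 50.

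**Does anything else at Visit 2 supply a test?** The Visit 2 text and the Visit 2 column of Appendix 1 agree that nothing does. Urine is collected, but for isoprostanes. As listed, it comes after randomisation, arterial stiffness, ECG and blood sampling. Even if that sample were tested, a visit run in the listed order would give the result after allocation, though before the forearm study.

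**How many women?** The protocol does not say. Entry starts at 30 years in the Healthy Group and 40 in the Stable CVD Group, runs to 80 in both, and each group is to have 36 completers. Women of child-bearing potential are possible in both groups, since the protocol schedules a test for them, but they are likely to be few.

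**The case against.** The strongest reply is that nothing here is an error. The visit text and Appendix 1 agree on one test, in a window of at most 28 days. Pregnancy is among the criteria reviewed again at Visit 2, and nothing forbids a test as part of that review. The supplement is a commercially available food product, few women are likely to be affected, and no result of the trial depends on the point. Much of this stands. The schedule is consistent, and testing at screening only is a choice that a protocol can make. What remains is that the second eligibility check cannot detect an unrecognised pregnancy, and that a simple test would let it do so.

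A reader might go further and infer that the larger gap at Visit 3, 56 to 91 days, is the more serious failing. The document does not support that. Pregnancy is an entry exclusion; the Withdrawal Criteria section names only inability to tolerate the study substance, and no criteria check is scheduled at Visit 3. The protocol thus sets no pregnancy rule after entry for an old test to breach. A test there that stopped the infusion would be a new rule, and it would cost a randomised participant's primary outcome, which recruiting another completer would not restore.

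A reader might also infer that the supplement is hazardous in pregnancy. The document says nothing to that effect, and no such claim is made here.

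Two practical objections also stand. The Visit 2 urine would have to be collected earlier than listed, and the 7-day lower limit is inferred rather than stated.

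**Conclusion.** The point holds for Visit 2, as a low-cost improvement and not as a contradiction. At randomisation and the first intra-arterial study the only pregnancy result is up to 28 days old, and at least about 7 days old if the home blood pressure readings are completed as written. An unrecognised pregnancy arising or becoming detectable in that interval would not be found by any scheduled test.

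This assumes that the schedule is followed as written and that no test is added informally at the Visit 2 check. The number of women concerned is unknown and probably small. Sample size, power, alpha and the analysis are untouched. For Visit 3, a repeat test is a sensible option that the sponsor may take or leave.

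**What to change.** In the Visit 2 text and in Appendix 1:
- add a urine pregnancy test at Visit 2 for women of child-bearing potential;
- move urine collection to the start of Visit 2, so that the result is known before randomisation and the forearm study;
- state that a woman with a positive result is not randomised.

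The cost is one dipstick per eligible woman, a small reordering of Visit 2 and a rare late exclusion. No extra visit or invasive procedure is needed. The isoprostane sample can serve if it leaves enough for a dipstick; the protocol gives no volume, so this is an assumption.

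Optionally, repeat the test before the Visit 3 infusion. If this is adopted, the protocol should say that a positive result means no infusion, and should accept that the participant's end-of-treatment primary outcome is then missing.
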